# Self-Myofascial Release Intervention and Mobile App in Patients With Hemophilic Ankle Arthropathy: Protocol for a Randomized Controlled Trial

**DOI:** 10.2196/15612

**Published:** 2020-07-31

**Keywords:** Hemophilic arthropathy, ankle, self-myofascial release, joint pain, functionality, randomized clinical trial

## Abstract

**Background:**

Hemophilic ankle arthropathy is manifested by degenerative functional alterations and chronic pain. Myofascial release techniques are used to treat soft tissue adhesions, relieve pain, and reduce tissue sensitivity.

**Objective:**

This study aims to evaluate the safety and efficacy of a protocol using self-myofascial release with a foam roller to be applied in patients with hemophilic ankle arthropathy.

**Methods:**

Patients with ankle arthropathy (N=70) will be recruited, enrolled, and assigned to one of two groups—experimental or control—in a 1:1 allocation ratio. Patients will be recruited from 5 centers in different regions of Spain. Patient data will be collected at baseline, posttreatment, and follow-up. The primary outcome will be frequency of ankle joint bleeding (self-reported). The secondary outcomes will be ankle range of motion (measured with a digital goniometer); joint pain (measured with a visual analog scale and an algometer); joint status (measured using the Hemophilia Joint Health Score); muscle strength (measured with a dynamometer); functionality of lower limbs (measured using the 6-minute walking test); activity (self-reported); and muscle flexibility (measured using the fingertip-to-floor test). The treatment program includes 11 exercises that must be administered bilaterally. A mobile app will be developed where each patient will be able to observe the exercises to be carried out. Each session will last 15 minutes with 5 physiotherapy sessions per week for a period of 3 months. It is expected that patients with hemophilia who receive the foam roller intervention will show improvement in mobility, pain, and status of the ankle joint; muscle strength; and function in the lower extremities.

**Results:**

The study has been approved by the institutional review board of the University of Murcia. Patient recruitment will begin in September 2020, and the intervention period will last until June 2021. Data collection will take place between September 2020 and October 2021.

**Conclusions:**

This protocol describes a randomized clinical trial to examine the safety and efficacy of a self-myofascial release intervention using a foam roller in patients with hemophilic ankle arthropathy.

**Trial Registration:**

ClinicalTrials.gov NCT03914287; http://clinicaltrials.gov/ct2/show/NCT03914287.

**International Registered Report Identifier (IRRID):**

PRR1-10.2196/15612

## Introduction

Hemophilia is a congenital coagulopathy characterized by a deficiency of a clotting factor (factor VIII in hemophilia A and factor IX in hemophilia B). Most clinical manifestations are musculoskeletal such as bruising and hemarthrosis. The recurrence of joint bleeding causes degenerative, progressive, and chronic joint deterioration (hemophiliac arthropathy); chronic pain; and a deteriorated perception of the patient's quality of life. Symptoms of hemophilic arthropathy include limited range of motion, decreased periarticular muscle strength, decreased proprioception, and chronic pain [1,2].

The ankle joint, a crucial component of locomotion, is one of the most affected joints (as are the knee and elbow joints) [3], imposing important functional and proprioceptive limitations. These limitations are the result of developing intra-articular alterations such as joint space narrowing, the development of osteophytes, bone deformities, or axial alterations [4]. Prophylactic treatment has been shown to be highly effective in the prevention of hemophilic arthropathy [5]; however, many patients, nevertheless, develop these sequelae as a result of late initiation of treatment, poor adherence to prophylaxis, or the development of inhibitors (antibodies to factor VIII or factor IX concentrates).

The treatment of hemophilic ankle arthropathy includes pharmacologic and orthopedic interventions with the aim of improving symptoms in the patient. The administration of anti-inflammatory and analgesic drugs [6], conducting synoviorthesis to remove the synovial membrane, and ultimately, arthrodesis of the ankle joint are the most common treatments [7].

Physiotherapy can play an extremely important role in the treatment of hemophilic ankle arthropathy. Manual therapy techniques [8], therapeutic exercise [9], or electrotherapy [10] have provided positive results in the control of chronic pain in patients with hemophilic ankle arthropathy.

The degenerative process, itself, is one of the intrinsic mechanisms affecting the fascial system, since it favors loss of elasticity and flexibility, and triggers a process of pathological cross-linking of collagen fibers. Fascial therapy aims to remove fascial tissue restriction through mechanical stimuli applied for 3 to 5 minutes in order to promote the piezoelectric effect in the crystalline matrix of the fascia [11]. The mechanical stimulus to the fascia (in the form of either pressure or tangential compression) triggers a secondary conjunctive cellular response and promotes cellular communication through piezoelectric and mechanotransduction mechanisms [12]. Although pilot and cohort studies [13,14] have proven that this technique is safe in patients with hemophilic arthropathy of the ankle, clinical studies need to be conducted with a large sample size in order to confirm that this technique is indeed suitable.

Fascia is the soft tissue component of the connective tissue matrix that extends through the human body forming a continuous three-dimensional composite of structural support throughout the body [15]. Myofascial release is a physiotherapy technique in which sustained pressure is applied in order to reduce restrictions of the fascia. Mechanical stimulation favors the readjustment of collagen fibers and improves the quality of movement, fluid circulation, and lymphatic drainage [16]. These changes can help break apart adhesions caused by processes such as scarring and fibrosis in the body. Myofascial induction is a manual physiotherapy technique that applies the principles of biomechanical loading of soft tissue and modification of neural reflexes through stimulation of the mechanoreceptors in the fascia to release fascial restrictions and restore healthy tissue [17].

Self-myofascial release with a foam roller is used to treat fascial adhesions and to restore the normal extensibility of soft tissues [18]. Self-myofascial release has similar effects to those provided by manual fascial release techniques. These benefits include easing muscle tension and stiffness, reducing pain, reducing inflammation, alleviating muscle spasms, and increasing joint mobility. Myofascial release techniques have been used to treat adhesions of the soft tissue, to relieve pain and tissue sensitivity, and to reduce edema and inflammation, while improving muscle recovery [19]. In self-myofascial release, patients use their own body weight and materials such as a foam roller to exert pressure on the affected soft tissues [20,21]. Scientific evidence has shown that these types of tools help improve the range of motion as well as pre and postexercise muscle performance [21,22]. The efficacy of these types of exercises to improve joint mobility has been tested in relation to improving mobility in knee flexion [20] and relative to improving ankle joint mobility [23].

The use of foam rollers for myofascial release is based on findings of postintervention changes to joint range of motion and pressure pain thresholds which may be due to a mechanical and neurophysiological responses [24,25]. The direct pressure of the roller may produce local mechanical and global neurophysiological effects that relax the tissues and attenuate pain in the targeted and surrounding area [26]. Local pressure from the roller may affect the viscoelastic properties of the myofascia which may be responsible for such changes within the tissue. Other mechanisms that may be involved include thixotropy (reduced viscosity when stress is applied), reduced myofascial restriction (from the breaking apart of physical adhesions), fluid-related changes (forced fluid displacement within the tissue), and cellular responses (elicited through mechanotransduction from the applied stress within the tissues) [24]. Researchers have also found that foam-rolling reduces arterial stiffness, increases arterial tissue perfusion, and improves vascular endothelial functions related to tissue relaxation [27].

The objective of this paper is to describe our approach to the design and implementation of a protocol for self-myofascial release using a foam roller for patients with hemophilic ankle arthropathy with the aim of reducing the frequency of joint bleeding; improving range of motion; reducing joint pain; and restoring functionality, structural integrity, muscle flexibility, and muscle strength.

## Methods

### Study Design

This study is designed as a randomized controlled multicenter clinical trial (ClinicalTrials.gov; NCT03914287) to establish the safety and efficacy of a physiotherapy intervention consisting of self-myofascial release using a foam roller. Once eligibility is determined, participants will be randomized to either the intervention (experimental) group or the control group.

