### Outcome Measures

Baseline assessments will be carried out at Hemophilia Association centers. Measurements will be performed by a physiotherapist who is unaware of patient group assignments.

After the treatment period and 3 months after completion, the patients included in both groups (experimental and control) will be re-evaluated by the same rater under the same conditions as their initial evaluation.

Dependent variables (range of motion, joint pain, functionality, joint state, muscle strength, muscle flexibility, and record of activity) will be measured at each study assessment (baseline, posttreatment, and follow-up). A 10-point visual analog scale will be used to evaluate patient perception of joint pain, ranging from 0 (no pain) to 10 (maximum perceived pain). An algometer (FPN100; Wagner Instruments) will be used for the assessment of pressure-induced pain (the amount of pressure at which the person perceives pain), both at the joint and at other body sites [28]. Pressure will be applied gradually at the site, increasing at rate of 50 kPa/s until the patient reports that the sensation is painful [29]. In patients with ankle arthropathy, bilateral measurements will be taken anterior to the lateral malleolus (ankle) [30] and at two other sites—the spinous process of the L5 vertebra and on the extensor carpi radialis longus muscle of the forearm (5 cm distal to the lateral epicondyle of the humerus) [28]. Using a portable instrument [31] for assessing physical activity, patient physical activity level (average number of steps per day, average distance per day, average amount of active time, and energy consumption) will be recorded. The Hemophilia Joint Health Score [32] will be used to evaluate the joint condition of knees, ankles, and elbows. It includes 8 items (inflammation and its duration, pain, atrophy and muscle strength, crepitus, and reduced flexion and extension) ranging from 0 to 20 points per joint (the higher the score, the greater the joint deterioration).

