### Intervention

Patients will continue their factor VIII or factor IX concentrate treatment as prescribed by their referring hematologists. Throughout the study, the prescribed pharmacologic treatment, dosage, and periods of substitute treatment of the participants will not be altered. Participants in the control group will receive no physical therapy using self-myofascial release and will continue with their usual routine of physical activity and exercise. Outcomes will be assessed under the same conditions as those of the experimental group.

At the beginning of the study, the main investigator will explain the characteristics of the intervention to be carried out to the experimental group. Each session will last approximately 15 minutes, with 5 physiotherapy sessions over a period of 3 months. Each patient will perform the interventions at home. Participants will have free access to the mobile app. Access to the platform will be approved after the patient signs the informed consent form. Once the study is complete, the contents of the app (Table 1) will be available on the website of the Hemophilia Physiotherapy research group (InHeFis).

The protocol for self-myofascial release of the lower limbs using a foam roller and solid ball massage, adapted to patients with hemophilic ankle arthropathy, will include self-myofascial release of the plantar, back of the leg, and hamstring regions, as well as adductor, abductor, and pelvitrochanteric muscles. Table 1 shows the physiotherapy protocol. Periodic follow-up will be performed, through phone calls and by SMS text messages, to answer questions from patients regarding the use of the app.

A mobile app (designed by the research group) will be used to demonstrate all the exercises in the self-myofascial release protocol. Each time the patient exercises, he or she will be able to watch a video explaining the characteristics of each exercise (time, repetitions, position, and action). This free app will also collect adherence data recorded as days of exercise by the participant.

Patient will need to have a suitable floor mat. A massage ball will be used for pressure point massage (solid ball massage), typically 40 mm to 50 mm in diameter, made of a hard polyurethane, but slightly padded. Two smooth low-deformability foam rollers (90 cm in length and 15 cm in diameter) will also be used.

**Table 1 table1:** Physiotherapy protocol using self-myofascial release for patients with hemophilic ankle arthropathy.

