### Data Analysis

The distribution of the sample, the changes after the intervention and follow-up period in each group, and the intra and interindividual effect will be analyzed. We will use the intent-to-treat method to include all individuals who were randomized in the final data analysis.

The statistical analysis will be carried out using SPSS statistical software (version 19.0; IBM Corp). The Kolmogorov-Smirnov test will be used to test for normality, and the Levene test will be used to test for homoscedasticity. If the conditions of normality and homoscedasticity are violated, nonparametric tests will be used.

Descriptive statistics (mean and standard deviation) will be calculated for all dependent variables. A one-way repeated measures analysis of variance will be used to compare the groups (experimental and control) at 3 assessment times (baseline, posttreatment, and follow-up). If the interaction is found to be significant, pairwise comparisons will be performed. The significance level will be set at α=.05. To control the error rate, Bonferroni correction will be applied. The results of the *F* test will depend on the significance of Mauchly sphericity. If significant, the Greenhouse-Geisser correction will be used. To assess clinical relevance, we will calculate the standard error of measurement and minimum detectable change for each dependent variable.

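### The article promises a safety conclusion, but its only named bleeding outcome is at the ankle and its only stated inference is a difference test, so it gives no basis for that conclusion

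*Protocol article*

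**What the plan says.** The Study Design section of the protocol article gives safety equal standing with efficacy: the trial is "to establish the safety and efficacy of a physiotherapy intervention consisting of self-myofascial release using a foam roller". The abstract's objective and conclusions also list safety, with the verbs *evaluate* and *examine*. The Discussion speaks of validating it.

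The abstract names one bleeding outcome: "The primary outcome will be frequency of ankle joint bleeding (self-reported". None of the secondary outcomes is a bleed or another safety event. The Introduction treats bleeding as an efficacy target, "with the aim of reducing the frequency of joint bleeding", and there speaks of joint bleeding without restricting it to the ankle.

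The Data Analysis section plans that "A one-way repeated measures analysis of variance will be used to compare the groups (experimental and control) at 3 assessment times", with pairwise comparisons if the interaction is significant and nonparametric tests if assumptions fail. "The significance level will be set at α=.05". It gives no margin, confidence-interval criterion or other rule for concluding safety. Outcome Measures lists the variables taken at each assessment: "Dependent variables (range of motion, joint pain, functionality, joint state, muscle strength, muscle flexibility, and record of activity". Bleeding is not among them, so it is not clear that the analysis of variance covers the primary outcome.

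The Intervention section says that the protocol "will include self-myofascial release of the plantar, back of the leg, and hamstring regions, as well as adductor, abductor, and pelvitrochanteric muscles". Table 1 adds the front of the ankle and the anteroexternal leg.

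**The concern.** Three parts of the article do not fit together: a safety objective, one bleeding endpoint at one joint, and a test built to find a difference.

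A difference test that is not significant does not show that bleeding is not increased. It may only reflect few events. The endpoint is also narrower than the exposure. Pressure goes on muscle from the foot to the buttock, and a calf or thigh muscle bleed is not an ankle joint bleed.

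The intervention is done at home by people with a clotting disorder, and the Discussion hopes for wide use. A safety statement that goes further than the data would err in the direction that harms patients.

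**Working it through.** **Inputs from the article.** 70 patients (Sample Size), "in a 1:1 allocation ratio" (Abstract, Methods), so 70/2 = 35 per arm. Data Analysis includes everyone randomized. With the stated 15% dropout, 35 × 0.85 = 29.75, about 30 per arm. Alpha is .05, and I take it as two-sided because sidedness is not stated.

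**The article's only computed size.** The national figure of 236 reproduces with a finite-population proportion formula, N = 612, 95% confidence, and assumed p = 0.5 and error 0.05:

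612 × 1.96² × 0.25 / (0.05² × 611 + 1.96² × 0.25) = 587.8 / 2.488 = 236.2, before any dropout allowance.

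That is a survey-precision calculation. It contains no bleed rate, effect, power or margin, so it says nothing about how well 70 patients can bound bleeding.

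**Assumptions.** Control rate λ from 0.25 to 2 ankle bleeds per patient over whatever period is counted; dispersion k of 0 or 1 (variance = mean + k × mean²).

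**Upper limit if the two rates are equal.** Var(log RR) = 2(1/λ + k)/n, and the upper 95% limit = exp(1.96 × √Var). For λ = 0.5, k = 1, n = 35: Var = 2 × 3/35 = 0.171, √Var = 0.414, exp(0.811) = 2.25.

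**Power of the two-sided .05 test for a true doubling.** Φ(ln 2/√V − 1.96), with V = [(1/λ + k) + (1/(2λ) + k)]/n. For the same case: V = 5/35 = 0.143, √V = 0.378, and Φ(1.834 − 1.96) = 0.45.

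| Bleeds per control patient | Upper limit, 35 per arm (k = 0 to 1) | Upper limit, 30 per arm (k = 0 to 1) | Power for a doubling, 35 per arm (k = 1 to 0) |
|---|---|---|---|
| 0.25 | 2.55 to 2.85 | 2.75 to 3.10 | 31% to 39% |
| 0.5 | 1.94 to 2.25 | 2.05 to 2.40 | 45% to 66% |
| 1.0 | 1.60 to 1.94 | 1.66 to 2.05 | 59% to 92% |
| 2.0 | 1.39 to 1.78 | 1.43 to 1.86 | 70% to 99.7% |

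At 0.25 the expected interval includes a doubling. At 0.5 it turns on the dispersion. At 1.0 and 2.0, with 35 per arm, it excludes a doubling.

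**Size needed if a margin were set.** Purely as an illustration, take a rate-ratio margin of 2.0, equal rates, 80% power and one-sided 0.025. Then n per arm = 2(1/λ + k)(1.96 + 0.84)²/(ln 2)². Over k = 0 to 1, the total before dropout is 262 to 328 at a rate of 0.25, 132 to 198 at 0.5, 66 to 132 at 1.0, and 34 to 100 at 2.0. Seventy patients meet it only at the higher rates with little overdispersion.

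**Rare events at other sites.** If none of 35 treated patients had a given kind of bleed, the one-sided 95% upper bound on its risk is 1 − 0.05^(1/35) = 8.2%.

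**The case against.** A reader might infer that the investigators will read a non-significant result as safety. The article does not say so: it sets no rule for concluding safety and presents bleeding as something to reduce. Nor does it call ankle bleeding its safety measure.

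A reader might also infer that bleeds elsewhere go unrecorded. That does not follow. This is a condensed article, and adverse-event recording and the design of the bleed form may sit in the full protocol. The Introduction's wider wording on joint bleeding leaves the intended scope open. The Hemophilia Joint Health Score covers knees, ankles and elbows, although it grades joint condition and does not count bleeds.

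A third tempting reading is that 70 patients can never support a safety statement. The table contradicts it: at one or two bleeds per patient with little overdispersion, a doubling could be excluded. Counting bleeds over the 3 months after treatment as well would also raise the counts.

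Finally, a margin is one legitimate approach but not the only one. Many trials of this kind describe safety, and a margin could be left to an analysis plan. The verbs *evaluate* and *examine* in the abstract are already softer than *establish*.

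All of this stands as a limit on the point. It leaves in place the mismatch between the stated objective, the one named bleeding endpoint and the stated test.

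**Conclusion.** The point holds in a limited form. The article declares safety as something to be established, names bleeding only at the ankle, and states only tests for difference. Followed as written, the named endpoint and test would not answer the trial's own safety question. A non-significant difference would not do so, and a muscle or other joint bleed at a rolled site falls outside every named outcome.

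The size is conditional. Every rate and dispersion used here is assumed. With 35 per arm and equal rates, the upper limit of the rate ratio runs from about 2.9 at low bleed rates down to about 1.4 at high ones. Because the article gives neither a rate nor a margin, it cannot claim the favorable end of that range.

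**What to change.** - Name all bleeds, by site and covering both joint and muscle, as a safety outcome. Collect them on the same form and schedule in both arms.
- Report the between-group bleed-rate ratio with its 95% confidence interval, and do not rest a safety statement on a non-significant p value.
- Change *establish* to *estimate* for safety, unless the sponsor prespecifies and justifies a margin that 70 patients can meet.

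The cost is one site field on the bleed report, if it is not already collected, some rewording, and a more modest safety claim.

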### Clinical Record and Selection Criteria

This study has been approved by the research ethics committee of the University of Murcia (2428/2019). Patients will be included if they have been diagnosed with hemophilia A or B, are 18 years of age or older, have been diagnosed with bilateral hemophilic arthropathy of the ankle (more than 3 points of joint damage on the Hemophilia Joint Health Score), and are on prophylactic or on-demand treatment with factor VIII or factor IX concentrates.

Patients will be excluded from the study if they are not able to ambulate; have been found to have inhibitors (antibodies to factor VIII or factor IX), have neurological or cognitive alterations that prevent them from understanding the questionnaires and physical tests, or choose not to give informed consent (have not signed the statement of informed consent).

